#### Primary outcomes

2.13.1

We will use univariate repetitive measurement deviation analysis with ISI scores and RMT before and the 10th day of treatment, 30th day of follow-up as the outcomes. A significant effect of group indicates that the ISI scores and RMT are different between groups after intervention.

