#### Withdrawal criteria

2.3.3

1.Violation of the inclusion criteria and clinical trial protocol or fulfillment of the exclusion criteria;2.Do not receive 10 consecutive treatment days or receipt of <20 rMS sessions;3.Serious adverse events;4.Loss to follow-up;5.Withdrawal of consent by the subject or a legal representative;6.Self-replacement of the treatment package that could affect the study results without permission from the investigator.

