### Statistical analysis

2.13

Data analysis will be based on intention-to-treat analysis and/or per-protocol analysis principle in the light of data missingness. We will also evaluate the group effect by comparing the analysis results between the above 2 data sets to evaluate robustness of our analytical results.

All data will be analyzed using SPSS23.0 (v23.0; SPSS Inc, Chicago, IL) by 3rd-party statistician. A *P* value <.05 will be considered as significant. Descriptive statistics will be performed with mean, standard deviation, maximum, minimum, and so on by groups and time.

Baseline characteristics of patients will be summarized by groups and compared with Chi-squared for categorical variables, and analysis of variance (ANOVA) (normal distributions) or Kruskal–Wallis test (non-normal distributions) for the continuous variables. Primary and secondary outcomes according to the measurement times are applicable to univariate repetitive measurement deviation analysis or ANOVA or Kruskal–Wallis test. If there is a violation of distribution assumption, appropriate transformation will be used.

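### The three-visit repeated-measures ANOVA in 2.13.1 usually drops anyone with a missing visit, so an intention-to-treat result becomes complete-case for them and loses measured day-10 data

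*Protocol article*

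**What the plan says.** Section 2.13.1 gives the primary method for ISI and RMT: "We will use univariate repetitive measurement deviation analysis with ISI scores and RMT before and the 10th day of treatment, 30th day of follow-up". I read this as a univariate repeated-measures analysis of variance over baseline, day 10 and day 30. The test of interest is the group effect: "A significant effect of group indicates that the ISI scores and RMT are different between groups after intervention".

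Section 2.13 sets the analysis principle: "Data analysis will be based on intention-to-treat analysis and/or per-protocol analysis principle in the light of data missingness". It treats "comparing the analysis results between the above 2 data sets to evaluate robustness of our analytical results" as the robustness check. The software is stated ("All data will be analyzed using SPSS23.0") but the procedure is not.

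Section 2.3.3 lists the reasons for withdrawal, among them "Loss to follow-up", withdrawn consent, serious adverse events and "Do not receive 10 consecutive treatment days or receipt of <20 rMS sessions". Section 2.8 adds as dropouts those who cannot tolerate the reduced stimulation intensity or whose rescue use exceeds a weekly limit. Section 2.7 allows rescue when symptoms are severe or fail to improve. Under 2.7.3 the waiting list is treated from day 11.

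**The concern.** A classical repeated-measures ANOVA works on complete records. A participant with baseline and day-10 scores but no day-30 score contributes nothing, not even to the day-10 comparison. That comparison matters most against the waiting list, because by day 30 those participants have been offered the positive-control treatment.

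Three things are at stake:

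- **Analysis set.** The named method does not deliver the intention-to-treat principle for people with an empty visit.
- **Robustness check.** To the extent that those who leave are not measured, both analysis sets rest on the same completers, so agreement between them tests little.
- **Bias.** If people doing badly leave more often, the completers in each arm are its better cases, and the arm losing most is flattered most. The rescue route makes this plausible: rescue is allowed when symptoms do not improve, and frequent rescue leads to dropout.

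**Working it through.** The plan has no figure of its own to reproduce. Section 2.11 gives 45 participants without an SD, effect size, power or dropout rate, so every rate, mean and SD below is an assumption.

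**Step 1: which exits leave a visit empty.**

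| Exit | Section | Empty visit? |
|---|---|---|
| Loss to follow-up | 2.3.3 | Yes, from that point |
| Withdrawn consent | 2.3.3 | Yes, from that point |
| Serious adverse event | 2.3.3 | Only if assessment stops |
| Too few treatment days or sessions | 2.3.3 | Only if assessment stops |
| Intolerance, or rescue above the limit | 2.8 | Only if assessment stops |

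The article does not say whether assessment stops in the last three rows.

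**Step 2: complete cases left.** With a fraction d lacking a day-30 value, complete cases = 45 × (1 − d). If loss is unrelated to outcome there is no bias, and the day-10 standard error grows by 1/√(1 − d) − 1.

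| d (assumed) | Complete of 45 | Increase in day-10 standard error |
|---|---|---|
| 10% | 40.5 | about 5% |
| 16.7% | 37.5 | about 10% |
| 25% | 33.75 | about 15% |

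The middle rate is 1 − 45/54. It uses the two totals in the article (54 in 2.1; 45 in 2.5 and 2.11) only as a convenient value. The article does not call the gap a dropout allowance.

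**Step 3: outcome-related loss, day-10 contrast against the waiting list.** Simulation of 6,000 trials, 15 per arm. Assumed ISI mean 17 at baseline; day-10 means 11 (HT7), 11 (r-DLPFC) and 16 (waiting list); SD 4 at baseline and 5 afterwards. The log-odds of a missing day-30 value rise with day-10 ISI by the slope shown, per 5 points. Overall loss is 16.7%.

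| Slope | All participants | Complete cases | Shrinkage |
|---|---|---|---|
| 1 | −4.99 | −4.50 | 1 − 4.50/4.99 = 10% |
| 1.5 | −5.00 | −4.11 | 1 − 4.11/5.00 = 18% |
| 2 | −4.97 | −3.85 | 1 − 3.85/4.97 = 23% |

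The waiting list loses 25% to 30% and each active arm 10% to 12.5%. This agrees with the overall rate: (25 + 12.5 + 12.5)/3 = 16.7 and (30 + 10 + 10)/3 = 16.7. At 25% overall loss the difference falls to between 4.3 and 3.6 points. A rerun with a within-person correlation of 0.5 gave matching figures (4.45, 4.10 and 3.81 at 16.7%; 4.29 to 3.57 at 25%). HT7 against r-DLPFC showed a bias of 0.0.

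**Step 4: unequal loss between arms, no true difference.** 400 simulated trials, SD 5, within-person correlation 0.6. One arm lost participants with high day-10 ISI; the other arms lost 5% at random. About 40 of 45 were complete. That is 45 − 40.1 = 4.9 lost, of which 0.05 × 30 = 1.5 came from the other two arms, leaving 3.4 of 15, or 23%, in the affected arm. The complete-case group effect over three visits was −1.3 ISI points (Monte Carlo standard error 0.08) in favour of the arm that lost its poor responders. A random-intercept mixed model on all observed values gave −0.03. That model kept baseline as an outcome, so it shows the principle and is not the exact model proposed below.

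**The case against.** The strongest reply is that the loss is inferred. The article names SPSS but no procedure, and a long-format or mixed fit would keep partial records. Imputation followed by the same ANOVA would keep everyone. Imputation rules commonly sit in a full protocol or analysis plan that is not shown, so their absence is no fault. Section 2.13 also lists plain ANOVA and Kruskal–Wallis as options by measurement time, and a day-10 ANOVA would use every day-10 score. All of this stands as a limit on certainty. It does not remove the point: 2.13.1 names the repeated-measures method specifically for the primary outcomes, and an unseen plan that used a mixed model would depart from that section.

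A reader might infer that nobody who leaves by any of the plan's exits can be in the intention-to-treat analysis, and that the two analysis sets would be almost identical. The article does not support this. A participant withdrawn for a serious adverse event, too few sessions, intolerance or rescue use may still be measured at all three visits. If so, the method keeps that person, and the two sets differ by exactly such people. Intention-to-treat is also offered only as an alternative to, or alongside, per-protocol.

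A reader might also infer that the noninferiority comparison of HT7 with r-DLPFC is biased. With equal loss in the two active arms it is not; that would need the further assumption used in step 4. Step 3 concerns the day-10 contrast alone, whereas 2.13.1 tests the group effect over three visits, although that effect against the waiting list shrinks in the same scenario.

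**Conclusion.** The point holds in conditional form. As written, the usual version of the named primary method drops any participant with a missing visit. An intention-to-treat result is therefore complete-case for those lost to follow-up or withdrawing consent, and for other dropouts if they are no longer assessed. This weakens the planned robustness comparison and can bias the contrast with the waiting list if leaving is related to outcome.

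No number in the article is shown to be wrong, and the real size is unknown. Under the assumptions above, about 34 to 40 of 45 remain at 10% to 25% missing. An assumed 5-point day-10 difference from the waiting list could shrink to roughly 3.6 to 4.5 points at 16.7% to 25% missing. Without outcome-related loss the cost is precision only. For a pilot this is an improvement worth making because it is cheap; it does not show that the trial fails.

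**What to change.** In 2.13.1, replace the univariate repeated-measures ANOVA with a linear mixed model for repeated measures (MIXED in SPSS 23), fitted separately to ISI and RMT:

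- **Outcomes:** the day-10 and day-30 values.
- **Fixed effects:** baseline value, arm, visit and arm-by-visit, so that the day-10 contrast is estimated directly.
- **Covariance:** unstructured, which with two visits means only three parameters.
- **Participants:** everyone randomised who has at least one post-baseline value, in the randomised arm. Those with none are still left out, so report their number by arm.
- **Sensitivity analysis:** the complete-case ANOVA.

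Also state that day-10 and day-30 assessments continue after treatment withdrawal where consent allows. This leaves the clinical exit and rescue rules as they are.

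The cost is some rewording and slightly more analysis work in software already named. No patients or visits are added; participants who stop treatment simply attend visits already scheduled. The downside is that a likelihood-based model in 45 participants needs a small-sample degrees-of-freedom correction, which should be named in the text. The model removes bias only where the loss is explained by values already observed, such as baseline or day-10 ISI.

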### Study group

2.5

Forty-five participants who meet the criteria with informed consents will be selected. The subjects will be randomly divided into 3 groups in a 1:1:1 ratio, namely the experimental group, positive-control group and waiting list control group, 15 cases in each group.

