#### Waiting-list control group

2.7.3

The participants in the waiting group will not be treated within 10 days during the study period, and then treated same as the positive control group from the 11th day.

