### Primary outcomes

2.9

The ISI scores for the severity of CI before and the 10th day of treatment, 30th day of follow-up. The RMT for excitability of the motor cortex before and the 10th day of treatment, 30th day of follow-up.

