### Estimation of sample size

2.11

This study is just a pilot study, which designed for efficacy evaluation and mechanism investigation of targeted therapy preliminarily before and after treatment as well as follow-up period. We will plan to enroll a total of 45 participants in this study.

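### The primary test reads the repeated-measures group effect as a post-treatment difference, but that effect averages in the pre-treatment baseline

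*Protocol article*

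**What the plan says.** Section 2.9 defines the primary outcomes as ISI and RMT at three times; for ISI the text is "The ISI scores for the severity of CI before and the 10th day of treatment, 30th day of follow-up". Section 2.13.1 fixes the model: "We will use univariate repetitive measurement deviation analysis with ISI scores and RMT before and the 10th day of treatment, 30th day of follow-up", all three named as the outcomes. The baseline value is thus a level of the response, not a covariate. The same section fixes the inference: "A significant effect of group indicates that the ISI scores and RMT are different between groups after intervention".

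Section 2.13 sets the threshold ("A *P* value <.05 will be considered as significant") and lists ANOVA and Kruskal–Wallis as general alternatives. Neither section names a group-by-time interaction, a baseline covariate, a change score or a post-baseline contrast for the primary outcomes.

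**The concern.** In a repeated-measures ANOVA the between-subject group test is the same as a one-way ANOVA on each participant's mean over all time levels. Here that mean is (baseline + day 10 + day 30)/3. A significant result says that the groups differ on this average. It does not say that they differ after treatment, which is what the plan reports it to mean. A post-treatment difference is shown by the group-by-time term or by a baseline-adjusted comparison at a post-treatment visit.

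Two things are at stake for both primary outcomes. A real effect is shrunk, because one of the three averaged visits has an expected difference of zero. And a chance baseline imbalance that persists through follow-up, a real possibility with 15 per arm, feeds directly into the test and would be reported as an effect of the intervention.

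**Working it through.** The protocol gives no power calculation, so there is no stated figure to reproduce.

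**Inputs from the protocol article**
- Three time levels in the model (2.13.1), with alpha 0.05 (2.13).
- Three arms, "15 cases in each group" (2.5), 45 in total (2.11). Section 2.1 says 54; that discrepancy does not affect this point.
- The waiting-list arm is untreated to day 10, "then treated same as the positive control group from the 11th day" (2.7.3).

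**Assumptions not in the protocol**
- SD 1 at each visit and equal correlation ρ between visits, taken as 0.3, 0.5 and 0.7.
- Both active arms better than waiting list by the same d (in SD units).

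**Step 1: what the group effect estimates.** Randomisation makes the expected baseline difference zero.
- Sustained effect: (0 + d + d)/3 = 2d/3.
- Waiting list fully caught up by day 30: (0 + d + 0)/3 = d/3.

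**Step 2: variances.**
- Three-visit mean: (1 + 2ρ)/3 = 0.533, 0.667, 0.800 at ρ = 0.3, 0.5, 0.7.
- Day-10 value adjusted for baseline: 1 − ρ² = 0.91, 0.75, 0.51.
- Day-10 value unadjusted: 1.

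**Step 3: noncentrality.** With two arms shifted by δ and one at zero, the squared deviations of the arm means sum to (2/3)δ². So λ = 15 × (2/3) × δ² / variance = 10δ²/variance. Power comes from the noncentral F distribution with 2 and 42 degrees of freedom (2 and 41 for ANCOVA).

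For d = 1:

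| Test | λ at ρ = 0.3 / 0.5 / 0.7 | Power |
|---|---|---|
| Group main effect, sustained (δ = 2/3) | 8.33 / 6.67 / 5.56 | 0.70 / 0.60 / 0.52 |
| Group main effect, full catch-up by day 30 (δ = 1/3) | 2.08 / 1.67 / 1.39 | 0.22 / 0.18 / 0.16 |
| Day-10 ANOVA, unadjusted (δ = 1) | 10 / 10 / 10 | 0.785 throughout |
| Day-10 ANCOVA on baseline (δ = 1) | 10.99 / 13.33 / 19.61 | 0.82 / 0.89 / 0.98 |

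For d = 0.8 with a sustained effect, the group main effect has power 0.50 / 0.41 / 0.35, against 0.62 / 0.71 / 0.87 for day-10 ANCOVA.

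**Step 4: behaviour with no treatment effect.** In 20,000 simulated trials with ρ = 0.5 and no effect, the group test rejected in 5.0%. Among the trials whose baseline values happened to differ significantly (also about 5%), 44.5% gave a significant group effect. The rule in 2.13.1 would report each of these as a difference after intervention.

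**The case against.** The strongest reply is that randomisation makes the group effect a valid 5% test. Its expected value is (d10 + d30)/3, which is zero exactly when the average post-treatment difference is zero, and the simulation confirms the error rate. When a real effect produces a significant result, the conclusion that the groups differ after treatment is true. This stands: the false-positive rate over all trials is not inflated, and the 44.5% is conditional on an imbalanced baseline. An unadjusted day-10 test would also be exposed to such an imbalance.

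A second reply is that the power gap is not all dilution. Averaging three visits also lowers the variance, so relative to a single unadjusted visit the standardised contrast is (2/3)d/√((1 + 2ρ)/3) = 0.91d, 0.82d and 0.75d. At ρ = 0.5 the gap splits into 0.60 to 0.785 from using day 10 alone and 0.785 to 0.89 from covariate adjustment. This also stands, but the group effect is below even the unadjusted day-10 test at each correlation shown.

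Third, the effect size and correlations are assumed, and with equal active arms the power figures concern active treatment against waiting list, not HT7 against r-DLPFC. That limits the figures. It does not limit the algebra: a sustained difference between the two active arms is shrunk by the same third.

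Fourth, the trial calls itself a pilot, and 2.13 allows ANOVA or Kruskal–Wallis by measurement time. But 2.13 still declares significance at 0.05, and the general list of tests does not alter the specific reading given in 2.13.1.

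**Conclusion.** The point holds and should be corrected before analysis. That the group effect tests a mean including baseline, and that a sustained difference is reduced by one third, follows from the model as written and needs no outside figure. The size of the power loss depends on the assumptions: at d = 1, a sustained effect and 15 per arm, it is 0.70 against 0.82 at ρ = 0.3 and widens to 0.52 against 0.98 at ρ = 0.7. These figures ignore the treatment of the waiting-list arm from day 11. Full catch-up by day 30 would lower the power of the group effect to about 0.22 to 0.16. The harm is lost power and misreading of baseline imbalance, not an inflated overall type I error.

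**What to change.** In 2.13.1, replace the group main effect by a comparison of the groups at day 10 adjusted for the baseline value of the same measure. This can be an ANCOVA, or a mixed model on the post-baseline visits with baseline, group, visit and group-by-visit. Report day 30 from the same model as a separate contrast, noting that the waiting-list arm has by then been treated. Delete the sentence that interprets the group effect. If the repeated-measures ANOVA is kept for description, base any inference from it on the group-by-time term. The adjusted model also supplies the HT7 versus r-DLPFC contrast on the right scale, although this change does not by itself provide a noninferiority test.

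The cost is analysis wording only. Baseline ISI and RMT are already collected, SPSS 23 fits both models, and recruitment, visits and treatment are unaffected.

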#### Secondary outcomes

2.13.2

Continuous outcome variables including Pittsburgh sleep quality index scores, Beck Depression Inventory-2nd edition scores, Beck anxiety inventory scores and Montreal Cognitive Assessment scores before and the 10th day of treatment will be analyzed with ANOVA or Kruskal–Wallis test. Categorical outcome variables in the patients’ diary, Chi-squared test will be used for comparison between groups.

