**Methods/design::**

This is a 3-armed randomized positive-controlled noninferiority clinical trial. We will allocate 45 subjects aged between 18 and 65 years old, diagnosed with initial chronic insomnia over 3 months to 3 groups randomly in a ratio of 1:1:1. Patients in the experimental group will be treated with rMS at HT7 acupoint while the others in the control group will be treated with rTMS at r-DLPFC or waiting treatment. All will be given rMS at HT7 or rTMS at r-DLPFC or no treatment for 10 days, and then received 20-day follow-up. Patients will be evaluated with the insomnia severity index and Pittsburgh sleep quality index for sleep state, Beck Depression Inventory-2nd edition scores for the depression state, Beck anxiety inventory scores for the anxiety state, and Montreal Cognitive Assessment scores for the cognition state before and the 10th day of treatment, 30th day of follow-up; study on mechanisms of rMS will be revealed through the resting motor threshold diversity of the motor cortex before and the 10th day of treatment, 30th day of follow-up. Baseline characteristics of patients will be summarized by groups and compared with Chi-squared for categorical variables, and analysis of variance or Kruskal–Wallis test for the continuous variables. Primary and secondary outcomes according to the measurement times are applicable to univariate repetitive measurement deviation analysis or analysis of variance, or Kruskal–Wallis test.

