### Study design

2.1

This is a single-center, randomized, positive-controlled, noninferiority clinical pilot trial. A total of 54 participants will be randomized into 3 groups at a ratio of 1:1:1. Participants in the treatment group will be treated with rMS at HT7 acupoint. Participants in the control group will be treated with rTMS at r-DLPFC or waiting treatment.

The whole study period is 35 days, including 5-day baseline observation, 10-day treatment, and 20-days follow-up. Subjects will be evaluated with scales for clinical efficacy before and the 10th day of treatment, 30th day of follow-up, and monitored by rMS/rTMS for therapeutic mechanism before and the 10th day of treatment, 30th day of follow-up (Fig. 1).

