### Secondary outcomes

2.10

Pittsburgh sleep quality index^[26]^ scores for the sleep quality of CI patients, Beck Depression Inventory-2nd edition scores for the depression state, Beck anxiety inventory scores for the anxiety state, and Montreal Cognitive Assessment scores for the cognition state before and the 10th day of treatment. Patients’ diary for tracking their mood, sleep, diet, adverse events, and others during the research. All the dropouts and causes will be documented in case report form.

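### The day-30 assessment of the four secondary scales is contradictory, and the tests named for them do not say how the baseline score is used

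*Protocol article*

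**What the plan says.** The article gives the times of the secondary scales in four places.

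- Abstract, Methods/design: the Pittsburgh sleep quality index (PSQI), Beck Depression Inventory (BDI-II), Beck anxiety inventory (BAI) and Montreal Cognitive Assessment (MoCA) are listed by name, ending with "Montreal Cognitive Assessment scores for the cognition state before and the 10th day of treatment, 30th day of follow-up".
- Section 2.1, Study design: "Subjects will be evaluated with scales for clinical efficacy before and the 10th day of treatment, 30th day of follow-up". No scale is named and none is excepted.
- Section 2.10, Secondary outcomes: the same four scales, ending with "Montreal Cognitive Assessment scores for the cognition state before and the 10th day of treatment", where the sentence stops.
- Section 2.13.2, analysis of secondary outcomes: the four scores "before and the 10th day of treatment will be analyzed with ANOVA" or a Kruskal–Wallis test.

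For comparison, Section 2.13.1 takes the primary outcomes to the last visit: "ISI scores and RMT before and the 10th day of treatment, 30th day of follow-up as the outcomes".

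On method, the general text of Section 2.13 is wider than Section 2.13.2: "Primary and secondary outcomes according to the measurement times are applicable to univariate repetitive measurement deviation analysis or ANOVA or Kruskal–Wallis test". Neither section mentions a baseline covariate or a change score for the secondary scales.

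**The concern.** Two schedules are stated for the same four scales, and both cannot hold. Under one, persistence of the effect on sleep quality, mood and cognition is measured twenty days after treatment. Under the other it is not. If the question stays open until the data are in, day-30 results on four scales can be reported or left out once they are known. In a trial where all subjects know their group (Section 2.12), time points fixed in advance are one of the few protections available.

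The second matter is the analysis. Every patient has a pre-treatment score, and the arms are small (15 each in Section 2.5), so chance imbalance at baseline can be sizeable. A plain ANOVA or Kruskal–Wallis test of day-10 scores leaves that imbalance in the estimate and forgoes precision. Because the general and the specific analysis text differ, at least three methods remain open for the same data.

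**Working it through.** **Schedule.** The places side by side:

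| Place | Scales covered | Day 10 | Day 30 |
|---|---|---|---|
| Abstract, Methods/design | PSQI, BDI-II, BAI, MoCA by name | yes | yes |
| Section 2.1 | scales in general | yes | yes |
| Section 2.10 | the four by name | yes | not listed |
| Section 2.13.2 | the four by name | yes | not listed |
| Sections 2.9 and 2.13.1 | ISI and RMT (primary) | yes | yes |

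The explicit conflict is the abstract against Sections 2.10 and 2.13.2; Section 2.1 supports the abstract only in general terms. The shorter schedule appears in both the definition and the analysis, next to primary-outcome text that does reach day 30, so it may be deliberate. Against that, the objectives at the end of the Introduction and the rationale in Section 2.11 both include follow-up. The text does not settle which was meant.

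**Waiting list at day 30.** Section 2.7.3 treats this arm like the positive control from day 11. A day-30 comparison with it is therefore not a comparison with no treatment.

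**Baseline.** The article has no figure to reproduce: it states no correlation, SD, target effect or power. The following is illustration.

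Inputs: n = 15 per arm (Section 2.5); significance level 0.05 (Section 2.13, "value <.05 will be considered as significant"), taken as two-sided. Assumed: correlation ρ between baseline and day-10 scores of 0.3, 0.5 or 0.7; equal SD at both times; a true pairwise difference of 0.8 SD.

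Variance relative to comparing day-10 scores alone:

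- ANCOVA: 1 − ρ²
- change score (equivalent to the group-by-time test with two time points): 2(1 − ρ)

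Approximate power: Φ(0.8 / (s·√(2/15)) − 1.96), where s is the square root of the relative variance. For day 10 only, s = 1, and 0.8/0.365 − 1.96 = 0.23, which gives 0.59.

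| ρ | ANCOVA variance | Reduction | Equivalent n per arm, 15/(1 − ρ²) | Power, ANCOVA | Change-score variance | Power, change |
|---|---|---|---|---|---|---|
| 0.3 | 0.91 | 9% | 16.5 | 0.63 | 1.40 | 0.46 |
| 0.5 | 0.75 | 25% | 20.0 | 0.72 | 1.00 | 0.59 |
| 0.7 | 0.51 | 49% | 29.4 | 0.87 | 0.60 | 0.81 |

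ANCOVA is at least as precise as either alternative at each ρ. The candidate methods also differ enough among themselves that the choice should be made beforehand. The variance ratios do not depend on n. The power figures are normal approximations and slightly favourable at this size.

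**The case against.** Three stronger readings are tempting, and the article does not support them.

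- *The baseline is ignored.* Section 2.13.2 lists the pre-treatment scores among the data, and Section 2.13 permits repeated measures for secondary outcomes, which would use them. What can be said is that the role of baseline is not specified, that the tests named in Section 2.13.2 do not adjust for it, and that the two sections differ.
- *Day-30 data would never be analysed.* Section 2.13 refers to analysis according to measurement times and to descriptive statistics by group and time. Day-30 scores, if collected, fall under both. They lack only an outcome-specific analysis.
- *Day 30 is the right schedule and Sections 2.10 and 2.13.2 are slips.* Those are the dedicated sections, and the abstract could equally be at fault.

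It can also be said that a condensed article may leave the handling of baseline to an SAP, and that under randomisation an ANOVA of day-10 scores is valid, only less precise. Both points stand. They make the baseline part an improvement worth adopting rather than an error. They do not remove the schedule conflict, because the article itself states both versions. It is also fair that the variance figures rest on an assumed correlation and on a day-10-only comparison that the article does not expressly state, and that they say nothing about the schedule.

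**Conclusion.** The schedule contradiction holds from the text alone: one time point on four secondary scales is both included and left out. The analysis point holds in a narrower form: the use of the baseline score is unspecified, the specific tests do not adjust for it, and the general and specific analysis sections disagree on method. The possible gain from adjustment, a 9% to 49% cut in residual variance for an assumed correlation of 0.3 to 0.7, is an illustration and cannot be fixed from the article. These are secondary outcomes in a declared pilot, so the change is advisable and cheap; it does not threaten the primary analysis.

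**What to change.** 1. Put one schedule for PSQI, BDI-II, BAI and MoCA in the abstract and in Sections 2.1, 2.10 and 2.13.2.
2. If day 30 is kept, state its analysis in Section 2.13.2, and say that the waiting list is not an untreated comparator at that visit.
3. Name one main analysis for these scales in Sections 2.13 and 2.13.2: ANCOVA of the day-10 score (and of the day-30 score, if kept) on group, with the baseline score as covariate, reported as pairwise differences with 95% confidence intervals.

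Cost: the analysis change is wording plus one degree of freedom per model. The day-30 visit already takes place for ISI and RMT, so keeping day 30 adds at most four questionnaires per patient, and nothing if they are already given then. If the change affects conduct of the study, Section 2.2 requires it to go to the ethics committee.
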